### 2.2 Final statistical analysis plan

A summary of our final statistical analysis plan is included in the current manuscript, under the heading of “Statistical Analysis”. A detailed version of this is below.

For our primary outcome of whole-body lean mass at 12 months after intervention commencement, we calculated that a target sample size of 100 participants would provide a power of 90% at a two-sided alpha level of 5%, allowing for up to 20% attrition as seen in previously-published weight loss interventions. Notably, attrition at 12 months in our current trial was 16% (to be detailed in the Results section), which fell within the attrition prediction used in our sample size calculation. Specifically, to detect a 5% difference in whole-body lean mass (e.g. 50.3 kg versus 53.0 kg, and assuming a variance of 5 kg), the effect size is 0.52, so at 90% power and  $P < 0.05$ , a sample size of 39 participants per group would be necessary, therefore with 20% attrition we would need 50 participants in each group. Further, based on studies in participants with obesity that elicited comparable weight losses to that anticipated from the SEVERE intervention in this trial, i.e. 12-20% of initial body weight over 12 months, the effect size to detect differences between interventions in the change in bone mineral density are large ( $> 0.8$ ), indicating that a sample of 20 per group would provide 90% power to detect significant ( $P < 0.05$ ) differences between interventions.

Statistical analyses were performed using SPSS Statistics Version 24 for Windows (IBM Corporation, New York, NY, USA). Statistical significance was accepted as  $P < 0.05$ . Fisher's exact tests were used to compare categorical demographic characteristics (age, ethnicity) and attrition between groups (i.e. SEVERE versus MODERATE). To compare continuous variables between groups at baseline (0 months), Mann-Whitney tests were used. All continuous variables were assessed for normality before analysis using histograms and P-P-plots. Where data were not normally distributed, a natural log-transformation was applied to obtain a normal distribution, although means and confidence intervals are reported on untransformed data.

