To compare longitudinal changes between groups, intention-to-treat analysis was performed using data from all participants originally randomized, using random effects linear mixed models. Mixed model analyses were used instead of standard repeated measures analysis of variance because of the likelihood that there would be dropouts and missed visits that preclude the use of the classical approach. Therefore, this model allowed for participants to have partial missing data and still be included without imputation. Intervention group and time (0, 4, 6, and 12 months for all parameters except for waist circumference, hip circumferences, and waist to hip ratio, which were assessed at all of these points plus at 0.25 and 1 months), were included as fixed effects, and participant was included as a random effect and included an intercept. Nominal

time was used, although measurements at 0 and 0.25 months were always done exactly 1 week apart, measurements at 1 month were done within  $\pm 2$  days from the exact date, measurements at 4 and 6 months were done within  $\pm 1$  week from the exact date, and measurements at 12 months were done within  $\pm 2$  weeks from the exact date. For all outcomes, baseline values of the relevant variable were added as a covariate in the analysis because when, by chance, there happens to be imbalance in the baseline covariate between groups, even when the two treatment groups are well balanced, adjusting for the covariates will (for linear models) give a more precise estimate of the treatment effect.

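### Baseline is both a month-0 response and a covariate in the between-group mixed model, so under the random-intercept covariance described the 12-month standard error is too small

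*Supplement*

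**What the plan says.** The primary endpoint is fixed in section 2.2 of the SAP: "For our primary outcome of whole-body lean mass at 12 months after intervention commencement", planned with "a power of 90% at a two-sided alpha level of 5"%.

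The same section describes the between-group model:

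- **Fixed effects:** "Intervention group and time (0, 4, 6, and 12 months for all parameters except for waist circumference", hip circumference and waist-to-hip ratio, which add 0.25 and 1 month. Month 0 is therefore a level of the response.
- **Covariates:** for every outcome, "baseline values of the relevant variable were added as a covariate in the analysis". Physical activity at each visit is added as well, and a secondary analysis adds weight at each visit.
- **Covariance:** participant is a random effect with an intercept, fitted by maximum likelihood. The covariance is called unstructured, but the sentence explains this as letting each individual's intercept vary.
- **Testing:** groups are compared at each time point only if the group-by-time interaction has P below 0.05. A Bonferroni adjustment follows, and its divisor is not stated.

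No sentence removes the month-0 rows or gives month 0 its own residual variance.

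**The concern.** In the month-0 rows the response is the covariate. Once the baseline slope is near 1, those rows have little left to explain. A random-intercept model assumes the same total variance at every visit, so it averages this artificially quiet visit with the real ones. The averaged variance then sets the standard error of every post-baseline group difference, including the primary one. At stake are the P value and confidence interval for lean mass at 12 months, and those of every other outcome put through this model.

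**Working it through.** **The plan's own figures.** The SAP states no error rate for this model beyond the nominal two-sided 5%, so there is nothing to reproduce on this exact point. The one input taken from its sample size paragraph is the spread: "e.g. 50.3 kg versus 53.0 kg, and assuming a variance of 5 kg" and "the effect size is 0.52". Since 2.7/5 = 0.54, while a true variance of 5 would give 2.7/√5 = 1.21, the 5 kg is read as an SD. (The stated 39 per group does not follow from a two-group formula: 2 × (1.96 + 1.282)² / 0.52² = 77.7, so 78. That is a separate matter.)

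**Assumed inputs.** The documents give no SD of change and no within-person correlation. The simulations used a total SD of 5 kg with equal correlations of 0.7–0.95, or SDs of change of 1–2.5 kg.

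**Step 1: residuals at month 0.** Write the model as Y(i,t) = a(t) + g(t)·group + β·B(i) + b(i) + e(i,t). At t = 0, Y equals B, and a(0) and g(0) are free. The residual is therefore (1 − β) × (B minus its group mean), with SD |1 − β| × 5 kg. At β = 0.79 that is 0.21 × 5 = 1.05 kg, and near β = 1 it almost vanishes. Simulated fits gave slopes of 0.79–1.00 and month-0 residual SDs of 0.13–1.07 kg, against 1.5–3.5 kg at later visits.

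**Step 2: rough effect on the standard error.** Suppose one visit in four contributes no variance and the other three share a common variance.

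- Four time levels: factor √(3/4) = 0.866. Then 1.96 × 0.866 = 1.697, and the two-sided error is 2 × [1 − Φ(1.697)] = 9.0%.
- Six time levels: factor √(5/6) = 0.913. Then 1.96 × 0.913 = 1.789, and the error is 7.4% (simulated: 7.7%).

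**Step 3: simulation with no 12-month difference.** Setting: 50 per group, missingness rising to 16% at 12 months, maximum likelihood, Satterthwaite degrees of freedom, 3,000 trials per scenario. Pointwise error at 12 months, before gate and Bonferroni:

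| Variance of change | As planned | Month 0 removed, random intercept kept | ANCOVA at 12 months |
|---|---|---|---|
| Constant | 9.7–10.1% | 5.0–5.3% | 4.8–5.4% |
| Growing with time | 18–23% | 11–15% | 4.9–5.3% |

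With constant variance, the model's standard error was 0.84–0.85 of the true SD of the estimate. Keeping month 0 and dropping the baseline covariate gave 4.5–5.1%.

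Further runs with 42 completers per group agreed. With post-baseline change correlations of 0.3, 0.5 and 0.7, the planned model gave 8.9%, 9.5% and 9.6%, against 5.1%, 5.4% and 5.7% with month 0 removed. Over all constant-variance runs the error was about 8–10% and the standard error ratio 0.84–0.88. Milder growth (SDs of 1.5, 1.8 and 2.2 kg) gave about 15–16%.

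**Step 4: with the interaction gate.**

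- *No difference at any visit, constant variance:* 2.6–2.9% in most scenarios, and 5.7% when post-baseline changes correlate 0.8.
- *No difference at any visit, growing variance:* 7.7–8.6%.
- *Assumed early difference (1.5 kg at 4 months, 0.75 kg at 6, none at 12), constant variance:* the gate opens in 91–96% of trials. The 12-month error is 9.5–10.0%, against 3.5–4.2% with month 0 removed.
- *The same early difference with Bonferroni dividing by 4:* 3.3–3.4% at a nominal 1.25%, about 2.7 times the intended level.

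**The case against.** The strongest reply is that 8–10% is not the error rate of the full planned procedure. Time points are tested only after a significant interaction, and then with Bonferroni. If the diets never differ and variance is constant, the gate alone usually brings the 12-month error near or below 5%. That stands, and a reader who inferred that the trial's final false-positive rate simply doubles would go beyond the documents. But the gate protects only while it stays shut. The Part 2 hypothesis in the protocol expects larger initial weight and fat losses on the very low energy diet and allows for larger lean losses. Outcomes Part 2 asks whether early differences persist. An early difference opens the gate and leaves the 12-month test exposed. Bonferroni by 4 keeps the rate below 5%, but well above its own target, and the SAP does not state the divisor. With two groups there is only one comparison per time point, so the divisor could even be 1. Neither step widens an interval to its nominal coverage.

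The second reply is that the SAP says unstructured. If a free residual matrix over all four visits was fitted, the single-variance argument fails. The SAP's own explanation, a varying intercept, points the other way. A free matrix would also be degenerate: a baseline slope of 1 sends the month-0 variance to zero and the likelihood has no bound. In that limit the analysis becomes a change-score comparison with an error of about 5%, but the written model would still need correcting.

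**Conclusion.** The point holds for the between-group model as written. Under the random-intercept reading and constant post-baseline variance, the standard error of the 12-month difference is about 12–16% too small. The pointwise, unadjusted error is about 8–10% rather than 5%. For waist, hip and waist-to-hip ratio it is about 7–8%, so the near-doubling does not extend to every outcome. The SDs and correlations are assumptions, but the result was stable across those tried.

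Three stronger readings are not supported:

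- The 15–23% seen when variance grows with time should not all be charged to using baseline twice. About 10–15% remains after month 0 is removed, because one variance is still forced on all visits.
- No bias in the estimated group difference has been shown. The fault lies in its stated precision.
- The within-group models in section 2.2 list no baseline covariate and are not affected.

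Because the primary P value and interval are touched and the remedy is cheap, this should be corrected.

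**What to change.** Use baseline once, in one of two ways:

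1. Restrict the response to post-baseline visits (4, 6 and 12 months, plus 0.25 and 1 month for waist, hip and their ratio). Fit group, visit, group-by-visit, baseline and baseline-by-visit.
2. Keep month 0 as a response with a common baseline mean in both arms, and drop the baseline covariate.

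In both cases, replace the single random intercept with an unstructured residual covariance across the response visits, so that the variance may differ by visit. Removing month 0 alone would not be enough if variance grows with time. A plain ANCOVA at 12 months, which held 4.8–5.4% in all scenarios, is a useful check on the primary result. Apply the same change to the weight-adjusted secondary analysis, and state the Bonferroni divisor.

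The cost is a revision of the SAP wording and a rerun in the same software. Intervals will become wider.

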## 1 Protocol

### 1.1 Original protocol

#### HUMAN RESEARCH ETHICS COMMITTEE (HREC)

#### Effects of fast versus slow weight loss on fat, muscle & bone in postmenopausal women

#### PROTOCOL

#### OVERALL HYPOTHESES AND AIMS

The worldwide prevalence of obesity is increasing at an alarming rate and is a major risk factor for type 2 diabetes and other diseases. An important aspect of curbing the impact of the obesity epidemic is providing effective long-term treatments. In clinical practice, meal replacement programs such as very low energy diets (VLEDs) are used with increasing frequency. Although such programs are safe and effective in the short-term (up to one year), few studies have assessed their long-term safety and efficacy. While there is evidence that the ketosis associated with VLEDs attenuates the appetite stimulating effect of weight loss, the fact that weight loss, notably when induced by VLEDs, induces adaptive responses that would tend to inhibit loss of – and promote regain of – adiposity (particularly central adiposity) while decreasing lean body mass and muscle strength and compromising skeletal health is of concern. Such changes include decreases in metabolic rate and physical activity, and neuroendocrine alterations such as increased circulating concentrations of cortisol, decreased thyroid function and decreased circulating levels of insulin like growth factor-1. Because of the known deleterious effects of these changes on body composition, it is vital to assess whether VLEDs have negative effects that could ultimately increase the risk of conditions such as diabetes, cardiovascular disease, sarcopenia and osteoporosis. This question is of particular importance given that individuals may use VLEDs for several months at a time repeatedly over many years in order to manage their weight.

**The overall aim of this project is to compare the consequences of weight loss via VLED versus less severe energy restriction on the strength of adaptive responses to energy restriction, as well as effects on adiposity (particularly central adiposity and hepatic fat), lean body mass, muscle size, muscle strength and bone mass for up to 3 years.**

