## SPECIFIC HYPOTHESES AND AIMS

### Part 1: Effect of VLED versus conventional diet on parameters that affect body composition

**Hypothesis:** Whilst the ketogenic state induced by VLED abates some of the adaptive responses that can oppose weight loss, promote regain and impair body composition, VLED will nonetheless induce stronger overall adaptive responses to weight loss than conventional diet.

**Aim:** To compare the effects of VLED versus conventional diet in obese adults on appetite, physical activity, metabolic rate, neuroendocrine status, circulating gut hormone concentrations, markers of bone turnover and sympathetic reactivity up to 12 months after commencement of each intervention. Groups will be matched by the amount of weight or fat lost (at differing time points) as well as by duration of intervention (at different levels of weight or fat lost). We will also compare the magnitude of these parameters before and 1 week after transition from the ketogenic VLED to the non-ketogenic conventional diet, to determine the effect of ketosis on these responses.

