weight loss at 3 months (at which point all participants will still be on the VLED, which results in ketosis due to its low carbohydrate and kilojoule content), participants will switch to a maintenance diet for 1 week followed by re-measurement at  $t = 3.25$  months. Fasting serum concentrations of ketones such as  $\beta$ -hydroxybutyrate will also be determined before and after this transition.

**Appetite.** Participants will be provided with a fixed (200 kcal) liquid meal (Optifast®, Nestlé Nutritionals, Vevey, Switzerland) at 9:00 am. Subjective measures of motivation to eat will be measured immediately before, after and at 1, 2 and 3 hours thereafter using the Electronic Appetite Rating System as described by [name].

**Physical activity.** Intensity and duration of daily physical activity will be measured using the Actigraph triaxial accelerometer worn on the waistband or on a belt. Accelerometry data will be collected during waking hours in the 7 days preceding each time point as previously described by [name]. Descriptive data will also be recorded in an activity diary, which will enable understanding of reasons for taking off the accelerometer (e.g. to swim or to sleep). Although all subjects will have the same standardized prescription to encourage physical activity, accelerometry and activity diary data combined with information from questionnaires (below) will provide insight as to possible effects of VLED or conventional diet on time spent exercising, in non-exercise activities or inactivity, and subjective measures of sleepiness.

**Resting metabolic rate** will be measured in the fasted state via indirect calorimetry using the TrueOne 2400 (Parvo Medics, Sandy, UT, USA) ventilated hood. Respired gases will be measured continuously for 30-min.  $VO_2$  and  $VCO_2$  will be converted to resting metabolic rate using the modified Weir equation as previously published by [name].

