As the degree of physical activity is known to influence measures of body composition, physical activity (expressed in metabolic equivalents of task, or METs) was added as a covariate, as measured at each of the timepoints. Maximum-likelihood estimation was used, and an unstructured covariance matrix was specified to account for the correlation between repeated measures over time by allowing the intercept for individuals to vary randomly. When the overall P value for the interaction between group and time was less than 0.05, Bonferroni adjustments were used to correct for multiple comparisons between groups at each time point. As a secondary analysis, the model was further adjusted for weight at each time point, because lighter individuals are known to have lower whole-body lean mass and BMD than heavier individuals. This was to determine if there was an effect of the interventions beyond that which would be expected due to weight loss.

Within-group changes were analysed with repeated measures linear mixed models. Intervention group and time were included in the model as fixed effects, and time as a repeated measure, with physical activity (METs) added as a covariate. Maximum-likelihood estimation was used, and an unstructured covariance matrix was specified. When the overall P value for the interaction between group and time was less than 0.05, Bonferroni adjustments were used to correct for multiple comparisons between time points and baseline (0 months) within each group.

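### The main intention-to-treat model adjusts for physical activity measured after randomisation, so it estimates an activity-adjusted contrast and not the total effect of diet assignment

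*Supplement*

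**What the plan says.** Section 2.2 of the final SAP names "our primary outcome of whole-body lean mass at 12 months after intervention commencement". It describes the between-group comparison this way: "intention-to-treat analysis was performed using data from all participants originally randomized, using random effects linear mixed models". The model terms are group, time, the baseline value of the outcome and activity: "physical activity (expressed in metabolic equivalents of task, or METs) was added as a covariate, as measured at each of the timepoints". The reason given is "As the degree of physical activity is known to influence measures of body composition". The only other between-group variant is a secondary model that adds current weight on top of METs. No model without METs, or with baseline METs only, is described.

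The protocol shown in section 1.1 places activity among the consequences of weight loss. Under Overall hypotheses and aims, on the adaptive responses to weight loss (with VLEDs singled out), it says: "Such changes include decreases in metabolic rate and physical activity". The Part 1 hypothesis is that "VLED will nonetheless induce stronger overall adaptive responses to weight loss than conventional diet", and the Part 1 aim lists physical activity among the measures to be compared between diets up to 12 months. The Physical activity paragraph expects accelerometry, diaries and questionnaires to give "insight as to possible effects of VLED or conventional diet on time spent exercising", even though both arms receive the same activity advice.

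**The concern.** An intention-to-treat comparison should estimate what being assigned to one diet and not the other does to lean mass, by whatever route. Activity at 4, 6 and 12 months is measured after assignment. If the diets change activity differently and activity affects lean mass, holding activity fixed removes that part of the diet effect from the estimate.

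There is a second problem. Illness or motivation, for example, may affect both activity and lean mass. Conditioning on activity then links diet to those unmeasured causes, and randomisation no longer protects the comparison.

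The primary result for lean mass is at stake, and so are the results for the other outcomes analysed with the same model, including bone mineral density.

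**Working it through.** No figure in the documents tests this point: they give no between-arm difference in METs and no slope of lean mass on METs. The check is therefore a reading of the specification, followed by illustrations on assumed values.

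**1. Is it the main model?** Yes. METs are in the model labelled intention-to-treat, and the one secondary variant keeps them and adds weight.

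**2. Is activity on the causal path?** Diet to activity: the protocol names reduced activity as an adaptive response, hypothesises stronger overall adaptive responses with VLED, and compares activity between diets. Activity to outcome: this is the SAP's own reason for the covariate. Together the two links make post-baseline METs a potential mediator by the documents' own account.

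**3. Is the SAP consistent?** It treats weight at each visit as a secondary adjustment, because that model asks about an effect beyond weight loss. METs at each visit raise the same issue but sit in the main model. The SAP's argument from chance imbalance and precision concerns baseline covariates and does not extend to later METs values.

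**4. How large could the mediated part be?** Inputs from the SAP: planning difference 53.0 − 50.3 = 2.7 kg, and spread 5 kg. The SAP calls the 5 kg a variance. It is read here as an SD, since 2.7 / 5 = 0.54 is close to the stated effect size of 0.52. Assumed inputs: arms differ in METs by *a* = 0.2 to 0.8 SD, and lean mass changes by *b* = 0.1 to 0.3 SD per SD of METs.

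Shift = 5 kg × *a* × *b*, with its percentage of 2.7 kg:

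| METs difference | *b* = 0.1 | *b* = 0.2 | *b* = 0.3 |
|---|---|---|---|
| 0.2 SD | 0.10 kg (4%) | 0.20 kg (7%) | 0.30 kg (11%) |
| 0.5 SD | 0.25 kg (9%) | 0.50 kg (19%) | 0.75 kg (28%) |
| 0.8 SD | 0.40 kg (15%) | 0.80 kg (30%) | 1.20 kg (44%) |

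If the activity path runs the same way as the total effect, an effect of 2.7 kg would be estimated as 2.6 down to 1.5 kg. If it runs the other way, the adjusted estimate would be too large by the same amounts.

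**5. What could a common cause do?** Assume no diet effect on lean mass and no effect of activity on it. Let an unmeasured cause load 0.5 SD on METs and 0.4 SD on lean mass. Within arms, METs have variance 0.5² + 0.75 = 1, and their covariance with lean mass is 5 × 0.4 × 0.5 = 1.0 kg. The fitted slope is therefore 1.0 kg per SD, and the adjusted contrast is 0 − 1.0 × *a*: −0.2, −0.5 and −0.8 kg for *a* = 0.2, 0.5 and 0.8. A simulation of 2,000,000 records gave −0.20, −0.51 and −0.81 kg adjusted, and about 0 unadjusted.

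**6. What happens when METs are missing?** In a standard likelihood mixed model, a visit row with an outcome but no covariate value is not used. The SAP's statement that partly missing data need no imputation covers a missing outcome. No rule is given for missing METs. A participant could therefore lose her 12-month lean-mass value from the analysis while her other visits still count.

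**The case against.** The adjustment is stated openly and has a reason. Both arms receive the same activity advice. The change log fixes the VLED phase at 4 months, eight months before the primary time point. The Part 1 hypothesis concerns adaptive responses overall, and the accelerometry text speaks only of possible effects, so the documents do not firmly predict a between-arm activity difference at 12 months. If METs prove similar between arms, the shift is small. The mediator evidence also comes from the original protocol, because the final one is only linked. The summary of changes, however, does not drop activity as a measure and adds pedometers.

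This limits what can be said about size, but it does not rescue the model: a primary analysis should not depend on the diets leaving activity unchanged when the trial sets out to test whether they do.

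A reader might infer four stronger things, none of which the documents support:

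- **That the estimate cannot be interpreted.** It can be read as an activity-adjusted contrast. It answers a different question from the effect of assignment.
- **That the adjustment hides lean-mass harm from VLED.** This requires lower activity in that arm and a positive slope, and the documents establish neither for 12 months.
- **That women are excluded, contrary to the claim to use all randomised participants.** Missing METs cost visit rows, not participants. No rate of missing METs is given, the source of METs is not named, and a screen before randomisation required candidates to show that they could wear the accelerometers and keep the diaries.
- **That the within-group model has the same fault.** It is not presented as the randomised contrast, so this argument does not carry over.

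**Conclusion.** The point holds. The main between-group model conditions on a variable measured after randomisation which, on the documents' own account, may respond to diet and affects the outcome. Its estimate is an activity-adjusted contrast, open to bias from unmeasured common causes, and no total-effect analysis is planned beside it.

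Size and direction cannot be determined from the documents. The 0.1 to 1.2 kg range rests on assumed METs differences and slopes and on reading 5 kg as an SD. Its upper end pairs the largest assumed difference with the steepest assumed slope. The common-cause figures of 0.2 to 0.8 kg rest on assumed loadings. The loss of 12-month rows is a secondary matter whose extent is unknown.

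**What to change.** Remove post-baseline METs from the primary model and from the other between-group intention-to-treat models. If an activity covariate is wanted, use the time 0 value only. Report the model with METs at every visit as secondary or exploratory, next to the weight-adjusted one, and say that it describes a contrast at a given level of activity. For that model, state the source of METs, what counts as a valid record, and how visits without one are handled.

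The cost is a short change to the SAP wording and a rerun on existing data. Some explained residual variance is lost. The loss should be small because the baseline value of each outcome stays in the model, but the documents do not allow it to be calculated.

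### The between-group model is called unstructured over time, but a random intercept alone implies equal variances and equal correlations, so the 12-month standard error may be wrong and is most likely too small

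*Supplement*

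**What the plan says.** All of the following is in section 2.2 of the Supplement, the final statistical analysis plan.

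- Groups are compared over time "using random effects linear mixed models". The random part is described in one clause: "participant was included as a random effect and included an intercept". No random slope, residual matrix across visits or robust standard error is named.
- The covariance is then described: "an unstructured covariance matrix was specified to account for the correlation between repeated measures over time by allowing the intercept for individuals", the sentence ending with that intercept varying at random.
- The response times are "Intervention group and time (0, 4, 6, and 12 months for all parameters except for waist circumference", hip circumference and waist-to-hip ratio, which have two further early visits. Month 0 is therefore a response row. For every outcome, "baseline values of the relevant variable were added as a covariate in the analysis".
- "Maximum-likelihood estimation was used"; REML is not mentioned.
- The within-group model is specified differently, with "time as a repeated measure, with physical activity (METs) added as a covariate" and an unstructured matrix.
- The result that matters most is the "primary outcome of whole-body lean mass at 12 months after intervention commencement".

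**The concern.** The text promises a covariance that is free over time, but the only mechanism it gives cannot deliver one. If the model is as written, the standard error of the 12-month group difference does not come from the spread of lean mass at 12 months. It comes from a variance averaged over all visits in the model.

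That average suits month 12 only if the variance given the covariates is the same at every visit. In a weight-loss trial, women may diverge or regain, and correlation with baseline usually weakens as visits become more distant. Weakening correlation is enough on its own: with constant raw variance σ² and correlation r with baseline, the variance given baseline is σ²(1 − r²), which rises as r falls. The primary confidence interval would then be too narrow.

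The plan also relies on this model to handle dropout without imputation. Likelihood methods under missing-at-random generally need a correct covariance, so the estimate could be affected as well as its standard error.

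**Working it through.** The plan reports no visit-specific variance, no correlation and no 12-month standard error, so it has no figure of its own to reproduce here.

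**1. What the stated model implies.** Take a random intercept with variance σb² and independent residuals with variance σe². Then:

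- variance at every visit = σb² + σe²
- correlation between any two visits = σb² / (σb² + σe²)

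That is 2 parameters. An unstructured matrix over 0, 4, 6 and 12 months has 4 × 5 / 2 = 10.

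**2. Effect on the 12-month standard error, month 0 removed.** With balanced data the fitted common variance is the mean of the visit variances, so

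- model SE = √(mean variance × 2/n)
- true SE = √(month-12 variance × 2/n)
- ratio = √(mean variance / month-12 variance)
- type I error of the unadjusted 12-month contrast ≈ 2[1 − Φ(1.96 × ratio)]

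Inputs: n = 50 × (1 − 0.16) = 42 per group, from the SAP's target of 50 and its 16% attrition. The SDs given baseline are assumptions.

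| Assumed SD at 4/6/12 months (kg) | Mean variance | Month-12 variance | Ratio | Type I error |
|---|---|---|---|---|
| 1.5/1.8/2.2 | (2.25+3.24+4.84)/3 = 3.44 | 4.84 | 0.84 | 9.8% |
| 1.5/2.0/3.0 | (2.25+4.00+9.00)/3 = 5.08 | 9.00 | 0.75 | 14% |
| constant | σ² | σ² | 1.00 | 5% |
| 2.2/1.8/1.5 | (4.84+3.24+2.25)/3 = 3.44 | 2.25 | 1.24 | under 2% |

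For the first row, model SE = √(3.44 × 2/42) = 0.40 kg and true SE = 2.2 × √(2/42) = 0.48 kg. Simulation of the same setting gave 0.404 against 0.476. Simulated type I error was 10-11% in the first row and 14-15% in the second.

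**3. The month-0 row.** At month 0 the response equals the baseline covariate, so its variance given that covariate is zero. If its fitted residual is taken as zero and the other three visits share variance σ², the mean over four rows is 3σ²/4 and the ratio is √0.75 = 0.87. Equal variance therefore fails as the model is written, without assuming that spread grows.

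**4. Simulation of the model as written.** There were 500 trials per pattern, 50 per group, ML and a baseline SD of 5 kg. Dropout reached 16% at 12 months (6% and 10% at 4 and 6 months assumed). METs were omitted. All correlations and change SDs are assumptions.

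| Pattern | Model SE / empirical SE | Ratio | Type I error | Ratio without month 0 |
|---|---|---|---|---|
| Raw data compound symmetric, r = 0.9 | 0.398/0.477 | 0.84 | 11% | 0.97 |
| Correlation decaying to 0.9 at 12 months | 0.309/0.482 | 0.64 | 20% | 0.75 |
| Change SD 1.5 at all visits | 0.269/0.326 | 0.83 | 11% | 0.95 |
| Change SD 1.0/1.2/1.8 | 0.245/0.391 | 0.63 | 20% | 0.73 |
| Change SD 1.0/1.3/2.5 | 0.308/0.541 | 0.57 | 24% | 0.67 |
| Change SD 2.0/1.8/1.5 | 0.321/0.327 | 0.98 | 6% | 1.12 |

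These type I errors are again for the unadjusted 12-month contrast, with a Monte Carlo error of about 1 point near 5% and 2 points near 20-24%. A 12-month ANCOVA on the same data held 5-6%. The as-written columns combine two features, the pooled variance and the month-0 row; the last column isolates the first.

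**5. The planned decision rule.** Visit-level comparisons are made only if the group-by-time P value is below 0.05, and then with Bonferroni adjustment. With month 0 removed and no group difference at any visit, simulation put the 12-month false-positive rate at about 1.5-2% for SD 1.5/1.8/2.2 and about 4% for 1.5/2.0/3.0.

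**The case against.** Three stronger conclusions are tempting, and the documents support none of them.

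**That the 12-month standard error is wrong and too small.** A reader might infer this from the algebra. It does not follow, because the documents give no visit variances. Without month 0, a constant SD makes the ratio about 1 and falling SDs make the test conservative. This objection stands and limits the claim to may be wrong, most likely too small. The lean is justified because month 0 is in the response as written, and none of the six patterns simulated that way gave a ratio above 1.

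**That the trial's false-positive rate for the primary endpoint is 10-15%.** Those rates ignore the interaction gate and Bonferroni step, which bring them down to the figures in step 5 when there is no effect at any visit. This objection also stands. It is not a full answer. The original protocol (Outcomes Part 2) anticipates that the very low energy diet may cause larger early lean losses, and a real early difference can open the gate whatever happens at 12 months. The Bonferroni step then still applies, but to a mis-sized standard error. The confidence interval is mis-sized in any case.

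**That no unstructured residual matrix was fitted.** The wording does not exclude one alongside the intercept, and no model code is shown. If one was fitted, the standard error is not restricted in this way. But the random intercept would then be redundant and the primary model misdescribed, so the text needs correcting on either reading.

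ML rather than REML biases variances downward only slightly with about 84 to 100 women. It is a minor point.

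**Conclusion.** The concern holds in limited form. The description contradicts itself: the covariance is called unstructured over time, while the stated mechanism gives compound symmetry, unlike the within-group model in the same section. On the literal reading, the 12-month standard error for lean mass rests on a pooled variance that includes an essentially zero-variance month-0 row. It may be wrong and is most likely too small.

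With month 0 removed, the ratio of model to true standard error is about 0.84 or 0.75 under the two assumed rising-SD patterns in step 2, about 1.0 with constant SD and above 1 with falling SDs. Direction and size rest on those assumptions. The structural point does not.

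**What to change.** Specify one between-group model:

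- responses at post-baseline visits only (4, 6 and 12 months), with the baseline value as covariate
- visit as the repeated effect within participant, with unstructured residual covariance
- no random intercept
- REML with Satterthwaite degrees of freedom

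Month 0 must leave the response. With baseline also a covariate, a slope of 1 and zero for the other month-0 terms fits that row exactly, and the unstructured likelihood is degenerate.

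Three visits need 3 × 4 / 2 = 6 covariance parameters, readily estimable with about 100 women. Waist, hip and their ratio have five post-baseline visits, hence 15 parameters, so name a fallback such as a heterogeneous first-order autoregressive or Toeplitz structure in case of non-convergence.

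If an unstructured residual matrix was already used, say so, and state how month 0 was handled.

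The cost is SAP wording, a rerun in the same software (already used for the repeated-measures within-group model) and a small loss of degrees of freedom.
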